### Pharmacokinetics Models

Non-linear mixed effects modeling (NONMEM) was used to analysis pharmacokinetic feature of Remimazolam Besylate for Injection in patients in ICU. Based on simulation of pharmacokinetic pattern, a recommended dosage and medication strategy for ERAS patients under mechanical ventilation in ICU is expected to carry out.

## Patients and Data Safety Monitoring

Besides routine critical care, a full-time certificated doctor and certificated nurse are responsible for observe patients and draw blood sample. A medical advisor team within the researcher team is 24-h online for any consulting related to the medication. All serious adverse events, as well as all non-serious adverse events that are unexpected and judged to be related to the study treatment, will be recorded in the study database and reported as required to Ethics Committee of Peking Union Medical College Hospital.

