## Introduction

### Background

Pain and anxiety are the most common physiological and psychological disorders associated with critical care patients. Organ dysfunction caused by severe diseases in ICU patients, combined with environment and various invasive treatments can produce strong pain and psychological stress, which may directly affect the respiratory, circulatory and immune functions of patients (1). Analgesia, sedation and humanistic care can reduce stress response, relieve tension, and reduce the incidence of delirium (2, 3). However, irregular analgesia and sedation treatments are not only ineffective, but may also cause adverse reactions.

Currently commonly used sedative drugs in clinical practice include midazolam, propofol, and dexmedetomidine. Midazolam has a good sedative effect and has little effect on the respiratory and circulation. At the same time, it can be antagonized by flumazenil. However, midazolam has a slower onset of action and a longer awakening time. As the infusion duration increases, it is easy to cause accumulation. Although propofol has a good sedative effect and can wake up quickly, it is prone to respiratory/circulation depression, and no antagonist was found suggest potential risks. Dexmedetomidine has a good sedative effect and has a small effect on respiratory, however, the pharmacological mechanism of dexmedetomidine determine its slow onset and negative effect on heart rate and blood pressure.

As a new type of sedative drug, Remimazolam can be rapidly metabolized by tissue esterase in the body to produce inactive metabolites, so that its sedative effect will quickly fade. In a phase I single-center randomized double-blind study, researchers found that Remimazolam can reach the peak blood concentration 1 min after intravenous infusion, the metabolism is rapid, and continuous infusion has almost no accumulation (4). Studies also show that Remimazolam has little effect on respiratory/circulation system. Blood pressure and heart rate fluctuate little during the injection of Remimazolam (5). The pharmacokinetics research on healthy volunteers shows its clearance is not related to weight, which provide more sedative option for high weight patients in ICU.

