## Outcomes

### Primary Outcomes

Validity endpoint is satisfaction rate of sedation, which equals to proportion of time in target sedation range (RASS score, 0 to −3) without use of rescue therapy of the total duration of study drug infusion. Safety endpoint is the incidence of hypotension (SBP < 90 mmHg), the incidence of hypoxia (SpO_2_ < 90%), and the incidence of bradycardia (HR < 75% baseline HR or HR < 50 bpm).

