### Secondary Outcomes

For validity evaluation, the secondary outcome includes incidence of delirium (subjects with delirium/total number of subjects × 100%) by 12 and 24 h after entering ICU. Time to weaning and extubation are recorded. Difficulty of nursing is evaluated by TISS-28 scoring system. RASS, BIS and PI are recorded every 30 min during medications. For safety evaluation, the secondary outcome includes 28-days survival, vital signs during medications, total dose and dose per kilogram body weight of analgesic and sedatives and incidence of rescue therapy in experimental group, side-effect report from usage of medications to 28 days after patients depart from intensive care unit. Side-effect is defined as hypotension, bradycardia, elevation of bilirubin, abnormal urine (Elevated urinary leucocyte/ketone body/bilirubin) in this study.

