## Allocation

Randomization will be carried out on the day of surgery immediately after the patients entered ICU and will be performed centrally through an online electronic data management system after confirmation with researchers that the patient is suitable for randomization. Participants will be randomly assigned to one of the two groups in a 1:1 ratio. Participants and their clients, researchers who are responsible for assessment, data recording and statistical analysis will be blinded to treatment assignment. The researchers will not be blinded to treatment assignment.

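### One filter (unexpected and judged related) governs both database recording and ethics reporting of non-serious adverse events, which leaves the general adverse-event comparison incomplete

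*Protocol article*

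**What the plan says.** Five sections of the protocol article bear on this point.

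- **Patients and Data Safety Monitoring.** All serious adverse events are recorded and reported to the ethics committee. Of the rest, "all non-serious adverse events that are unexpected and judged to be related to the study treatment, will be recorded in the study database", and the same sentence sends them to the ethics committee.
- **Primary Outcomes.** The safety endpoint consists of hypotension, hypoxia and bradycardia, each defined by a numerical threshold. Hypoxia appears as "the incidence of hypoxia (SpO_2_ < 90" per cent). None of the three depends on expectedness or causality.
- **Secondary Outcomes.** "Side-effect is defined as hypotension, bradycardia, elevation of bilirubin, abnormal urine". The collection period is fixed as "side-effect report from usage of medications to 28 days after patients depart from intensive care unit". Vital signs are collected during medication, and delirium by 12 and 24 hours after ICU entry.
- **Harms.** Researchers report to the ethics committee and the medical department when a major clinical event or a side-effect occurs. No condition of expectedness or relatedness is attached.
- **Allocation.** Those responsible for assessment, data recording and analysis are said to be blinded. The next sentence reads "The researchers will not be blinded to treatment assignment". The Abstract calls the trial open-label.

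**The concern.** A test of whether an event is unexpected and related is suited to deciding what must be reported to an oversight body. Here it also decides what enters the database. Anything it removes is lost to the analysis and cannot be recovered later.

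This matters because the Objectives hypothesise non-inferior safety as well as non-inferior efficacy, and the Abstract says that few trials have compared the new drug with propofol. The general adverse-event profile is therefore part of what the trial should deliver.

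Both conditions also rest on judgement. What counts as expected depends on what is already known about a drug, and more may be known about an established comparator than about a new one. The same non-serious event could then be dropped in one arm and kept in the other.

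The side-effect list only partly compensates. It omits hypoxia, although the Background says of propofol that "it is prone to respiratory/circulation depression".

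**Working it through.** The plan gives no figure on this point, so the check sets the passages side by side.

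**Step 1. What the recording sentence keeps.** A non-serious event is either expected or unexpected, and judged either related or unrelated, which gives 2 × 2 = 4 combinations.

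| Non-serious event outside the named outcomes | Recorded under the sentence? |
|---|---|
| Unexpected, related | Yes |
| Unexpected, unrelated | No |
| Expected, related | No |
| Expected, unrelated | No |

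One combination of four is recorded. This counts categories, not events. The documents do not say how many events would fall in each.

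**Step 2. What bypasses the filter.** Hypotension, hypoxia and bradycardia enter as primary safety endpoints. Raised bilirubin and abnormal urine enter as side-effects, and delirium as a secondary outcome. Vital signs during medication, 28-day survival, and times to weaning and extubation are also collected regardless. The gap in Step 1 is therefore confined to event types outside these outcomes.

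**Step 3. Primary safety events against the side-effect list.**

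| Event | Primary safety endpoint | Side-effect list (to 28 days after leaving ICU) |
|---|---|---|
| Hypotension | Yes | Yes |
| Bradycardia | Yes | Yes |
| Hypoxia | Yes | No |
| Raised bilirubin | No | Yes |
| Abnormal urine | No | Yes |

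Hypoxia is the only one of the three primary safety events missing from the list with the long window. Primary Outcomes states no collection period for it, and vital signs are tied to medication. A non-serious hypoxic episode after the infusion ends, if expected or judged unrelated, has no stated route into the data.

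**Step 4. Safety Monitoring against Harms.** Take a non-serious, expected episode of hypotension. It is on the side-effect list, so Harms has it reported to the ethics committee. Under Patients and Data Safety Monitoring it is not unexpected, so that sentence does not have it reported. Both rules cannot be the operative one.

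**Step 5. Who applies the conditions.** No section names the person who judges relatedness or expectedness. Allocation says both that assessors and data recorders are blinded and that researchers are not. The documents therefore do not settle whether these judgements are made blind.

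**The case against.** The strongest reply is that the recording sentence does not contain the word only. It can be read as a minimum for reportable events, with fuller recording rules in the complete protocol, which Dissemination says is available on request. A condensed article may fairly leave such detail out. This stands in part: the full protocol may record more. But the article does not leave the matter open. It states which non-serious events go into the database, and a reader following it would leave the others out.

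Second, much of the safety comparison never meets the filter (Step 2), and Data Management describes bedside monitors, ventilators and blood gas analysers feeding a central server. This stands, and it limits the point to events outside the named outcomes and to hypoxia after treatment.

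Third, differential filtering by arm is a possibility rather than a demonstrated effect. The documents give no list of expected events for either drug, so neither direction nor size can be derived. This also stands.

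A reader might infer two stronger claims. One is that unblinded staff judge causality. The open-label label and one sentence under Allocation suggest it, but the preceding sentence says the opposite for assessors and data recorders, and the documents do not name who assesses causality. The other is that the safety comparison misses hypoxia. It does not, because hypoxia is compared as a primary endpoint.

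**Conclusion.** The point holds in a limited form. As written, the recording rule drops non-serious adverse events that are expected or judged unrelated and are not named outcomes. The general adverse-event comparison is then incomplete, and the loss could differ between arms. In addition, Patients and Data Safety Monitoring and Harms conflict on ethics reporting, and the side-effect list does not match the primary safety endpoint on hypoxia.

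No size can be attached, since the documents give no expected adverse-event rates and unrecorded events leave no trace. The primary safety comparison of hypotension, hypoxia and bradycardia is not put in doubt by this point. The conclusion assumes that the recording sentence is applied as it stands and that no fuller rule elsewhere overrides it. It is a worthwhile, inexpensive improvement rather than a flaw that undermines the trial.

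**What to change.** 1. Record all adverse events in both arms, over the side-effect window already set, whatever their expectedness or judged relation. Hold both judgements as data fields, not as conditions of entry.
2. Keep the unexpected-and-related condition only as a trigger for reporting to the ethics committee, and reconcile it with Harms so that one reporting rule applies.
3. Add hypoxia to the side-effect list under Secondary Outcomes so that it matches Primary Outcomes.
4. Name who judges relatedness and expectedness, and reconcile the two blinding statements under Allocation for that role.

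The cost is a few sentences of protocol text and modest extra data entry for 84 patients, for whom a full-time doctor and nurse are already assigned to observation. If the full protocol already records all events, only the wording needs to be aligned.

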## Harms

The risks and harms associated with this study are low. The risk of a breach of confidentiality is small and all possible efforts have been taken to ensure the security of study data and minimize the risks of accidental disclosure of identifiable data elements. The medical risks for participation in this study do not go beyond those risks typically associated with sedation treatment in in routine clinical care. Beyond the study consent, patients will also undergo standard procedural consent to discuss the risks and benefits of this clinical trial. If major clinical events or side-effect occurs, researchers will report to ethics committee and medical department of Peking Union Medical College Hospital. A quick response team will be formed before the clinical trial begin. Once major clinical events or side-effect occur, the quick response team will handle the clinical treatment, including emergency rescue and injuries assessment. Besides, researchers will purchase clinical trial insurance for each subject, which may give compensation for any harm happened in this clinical trial.

## Ethics Approval and Informed Consent

Ethical approval on this protocol (v1.2) was obtained on 23rd March 2021 by the Ethics Committee and Medical department of Peking Union Medical College Hospital (20-JS-2814). Any substantial amendment made to the protocol by the coordinating investigator is sent to the Ethics Committee of Peking Union Medical College Hospital for approval, prior to implementation. All participants will give written informed consent prior to data collection and medication.

## Dissemination

Study results will be submitted for publication in peer-reviewed medical journals and presented to patients, healthcare professionals, and the public during (inter)national meetings. The full study protocol and the informed consent form are available from the corresponding author. After study completion, the participant-level dataset and statistical code will be available on reasonable request.

## Discussion

To our knowledge, this is the first clinical trial that investigate availability and safety of Remimazolam Besylate as sedatives in ERAS patients under mechanical ventilation in ICU, especially for process of weaning and extubation of mechanical ventilated patients. Compared with midazolam, Remimazolam Besylate has a short half-life period (4). It is an ester-based drug that rapidly hydrolyzed in the body by tissue esterase to an inactive carboxylic acid metabolite (12), which may relieve the burden of liver and kidney. Hence, unlike propofol and midazolam, physicians don't have to consider accumulation effect of sedatives.

## Ethics Statement

The studies involving human participants were reviewed and approved by Ethics committee of Peking Union Medical College Hospital. The patients/participants provided their written informed consent to participate in this study. Written informed consent was obtained from the individual(s) for the publication of any potentially identifiable images or data included in this article.

